**Methods:**

The PTA-DFS Study is a randomised controlled monocentric trial including individuals with T2D and DFU, aged > 18 years with haemodynamically relevant chronic LAS. The primary study endpoint is to investigate the impact of the early PTA within 48 h on wound-healing assessed by wound area changes after PTA using a 3D-camera with artificial intelligence (AI)-based wound-analysis-system. The secondary endpoint is the effect of early PTA on the combined occurrence of major adverse limb (MALE) and safety-related cardiac events (MACE) over 12 month post-angioplasty using time-to-event analysis. Additional secondary outcomes are time to complete wound healing, major amputation rate and the need for new revascularization. Explanatory variables for wound healing are wound microbiome changes using whole-genome sequencing and oxygen saturation of the wound environment measured using near-infrared spectroscopy. Data will be collected at baseline, 24 h, 1, 2, 3, 6, and 12 months after PTA. Diabetic kidney disease, distal symmetric polyneuropathy, retinopathy, cardiomyopathy, LAS will be assessed by laboratory analyses, clinical scores, AI-based fundus photography, echocardiography, duplex sonography, and pulse oscillography.

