**Fig. 1 Fig1:**
[figure not shown]
Timeline. The figure shows follow-up visits at respective time points during the study period. The specified times of the respective follow-up examinations refer to the time after the PTA. PTA = Percutaneous transluminal angioplasty, PAD = Peripheral arterial disease, T2D = Type 2 diabetes, DFU = Diabetic foot ulcer, RCT = Randomised controlled trial

The primary endpoint of the PTA-DFS Study is to assess the effect of early PTA on wound healing in T2D participants and chronic ischemic DFU. Wound healing is measured by the reduction of 3D wound area, assessed using clinical grading and 3D-camera analysis with AI-based evaluation of wound length, width, and depth. The secondary endpoint is the combined incidence of MALE and MACE post-angioplasty between early and elective PTA treatment, time to complete wound healing, major amputation rate and the need for new revascularization. Explanatory variables for the primary endpoint are differences in quantitative shifts in bacterial taxa with different oxygen requirements (aerobes, anaerobes) (Fig. 2). These shifts post-PTA will be analysed using appropriate statistical methods, such as Generalised Linear Mixed Models (GLMMs), accounting for treatment group (early PTA vs. elective PTA), bacterial taxa, and time, with random effects to adjust for individual variability. Another explanatory variable for wound healing is the change in oxygen saturation in the wound environment, measured by multispectral near-infrared spectroscopy (NIRS). These outcomes will be analysed using Cox proportional hazard models using time-to-event outcome for MALE/MACE events, adjusting for baseline covariates to evaluate the effectiveness of early PTA compared to standard treatment.

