### Statistical methods and power calculation

The primary endpoint focuses on the difference in changes of wound area (delta wound area at first - last visit) in T2D participants after early PTA compared to individuals with standard PTA. For the primary—change in wound area after early PTA—and secondary endpoint—combined incidence of MALE and MACE—a power calculation was performed. Assuming a medium effect size (Cohen's d = 0.4), corresponding to 0.4 standard deviations of the difference in delta wound area and difference in time-to-event from baseline to last visit between groups, a sample size of n = 100 per group (total n = 200) is required to achieve 80% power at alpha = 0.05.

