One explanatory variable evaluates the effect of early PTA on wound microbiome dynamics. This objective aims to measure the beta-diversity changes of the wound microbiome, assessed via whole-genome sequencing and analysed using Bray–Curtis distances. In detail, taxonomic profiles from whole-genome sequencing of the wound microbiome will be generated using bioinformatics scripts. The sequencing data, produced via the Oxford Nanopore platform [36] will be analysed with Kraken2 [37] and minimap2 [38] based on a custom database including protozoan, fungal, and viral sequences. Visualisations for comparing metagenomic composition across taxonomic levels will be generated with custom scripts. Principal coordinate analysis based on Bray–Curtis distances will assess sample clustering, with the entire workflow provided as a reproducible Snakemake pipeline [39]. Effect sizes are based on expected changes in Bray–Curtis distances for beta-diversity. Nominal variables will be compared using the Chi-Square Test and Fisher's Exact Test where appropriate. Relationships between variables (e. g., changes in wound microbiome or local microcirculation and wound healing or complications) will be assessed using partial Pearson or Spearman correlation coefficients, with adjustments for confounders and multiple testing via the Bonferroni or Benjamini–Hochberg method. The standardised mean difference (Cohen's d) will be used for power analyses due to the lack of preliminary data on changes of ulcer area and combined incidence of MALE/MACE after early PTA. Changes in beta-diversity of the wound microbiome, will be analysed using Generalised Linear Mixed models with fixed effects including treatment group, bacterial taxa, time, and random effects to account for patient variability. Interaction terms will assess differential effects between treatment groups. The secondary endpoint includes combined MALE and MACE incidence post-angioplasty. Oxygen saturation in wound environment is measured as another explanatory outcome potentially linked to wound healing. Additional outcomes will include an evaluation of risk factors such as comorbidities (severity of anaemia and stages of chronic kidney disease), severity of insulin resistance, DSPN, the duration of hospital stay and interactions with medications, including antibiotics and antithrombotic therapies. Risk endpoints include the incidence of MALE, progression of diabetic complications (e.g., neuropathy), and hospital stay duration. These will be analysed using survival analysis methods and logistic regression to evaluate risk/benefit ratios. Multiplicity will be addressed as follows: The primary outcome will be analysed at a two-sided significance level of 0.05 without adjustment. For the prespecified family of confirmatory secondary outcomes, the family-wise error rate will be controlled at 0.05 using the Holm–Bonferroni procedure. For these outcomes, raw and adjusted p-values as well as corresponding adjusted 95% confidence intervals will be reported. Exploratory outcomes will not be adjusted for multiplicity and will be clearly identified as exploratory. Safety outcomes will be reported descriptively. The interaction effects of antibiotics, PTA timing, and concomitant antithrombotic treatments on both primary and secondary endpoints will be assessed using logistic regression models and subgroup analyses. Time-to-event clinical endpoints will be analysed with Kaplan–Meier survival curves, while covariate adjustments will be incorporated using Cox proportional hazards models. Correlation analyses (partial Pearson or Spearman coefficients) will account for confounders and include multiple comparison corrections via Bonferroni or Benjamini–Hochberg adjustments. Categorical variables will be compared using Chi-Square or Fisher's Exact Tests, while continuous variables will be analysed with Wilcoxon rank-sum tests or Student's t-tests, as appropriate. Two-tailed p-values below 0.05 will be considered statistically significant. Missing data will be summarised by variable, time point, and treatment arm, and patterns of missingness will be described graphically and statistically. The primary analysis will employ multiple imputation by chained equations (MICE; m = 20 imputations) under the assumption of missing at random (MAR). The imputation model will be specified to be congenial with the planned analysis and will include treatment arm, relevant baseline covariates (e. g., age, sex, ulcer duration, ulcer size, Wagner grade, HbA1c, infection status), and outcome variables. Continuous variables will be imputed using predictive mean matching, binary variables will be analysed via logistic regression, and ordinal variables will be analysed using proportional-odds models. Estimates will be combined using Rubin’s rules. Sensitivity analyses will include (i) complete-case analysis, (ii) best–worst and worst–best case scenarios, and (iii) a delta-adjusted pattern-mixture model to assess departures from MAR and exploring missing not at random (MNAR). All statistical analyses will be performed using the R Version 4.4 and SPSS for Windows 23.0 (SPSS Inc., Chicago, IL, USA). Figures are created with GraphPad Prism, Version 7.01 (GraphPad Software, Inc., La Jolla, CA, USA) or R, and Graphical abstracts using BioRender.com.

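### Two supportive analyses name models that do not fit their outcomes: logistic regression for interactions on continuous and time-to-event endpoints, and a taxa term in the beta-diversity model

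*Protocol article*

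**What the plan says.** **Endpoints.** Statistical methods and power calculation defines the primary as a continuous quantity: "The primary endpoint focuses on the difference in changes of wound area (delta wound area at first - last visit". It powers this with Cohen's d and states no responder cut-off. The Abstract (Methods) has the combined MALE/MACE endpoint assessed "over 12 month post-angioplasty using time-to-event analysis". The text after Figure 1 names "Cox proportional hazard models using time-to-event outcome for MALE/MACE events". The statistical section also uses a looser wording: "The secondary endpoint includes combined MALE and MACE incidence post-angioplasty".

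**Interactions.** The statistical section states: "The interaction effects of antibiotics, PTA timing, and concomitant antithrombotic treatments on both primary and secondary endpoints will be assessed using logistic regression models", plus subgroup analyses. The very next sentence reads: "Time-to-event clinical endpoints will be analysed with Kaplan–Meier survival curves, while covariate adjustments will be incorporated using Cox proportional hazards models".

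**Microbiome.** The statistical section has beta-diversity "analysed using Bray–Curtis distances" and then says: "Changes in beta-diversity of the wound microbiome, will be analysed using Generalised Linear Mixed models with fixed effects including treatment group, bacterial taxa, time", with random effects for patients. The text after Figure 1 gives a generalised linear mixed model with group, taxa and time for a different response, namely quantitative shifts in taxa grouped by oxygen requirement.

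**Medication data.** Under Questionnaires, concomitant medication is collected at V0 and at V2 to V6. Main exclusion criteria lists antibiotic therapy less than 2 weeks before intervention, with the qualifier that this is for the microbiome measures.

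**The concern.** A logistic model needs a yes/no outcome. The primary endpoint is not one, so someone would have to choose a threshold for wound-area change that the plan does not give. That is an avoidable analyst choice in a trial where participants and physicians are unblinded. For MALE/MACE, a logistic model ignores when events happened and how long each patient was followed, and it competes with the Cox model named in the next sentence.

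The medication interactions raise a second question: when is drug use measured? If it is use after randomisation, it may itself depend on arm and wound state, because the elective arm can wait up to 6 weeks for PTA. Arm comparisons within strata of such use are not randomised comparisons.

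For the microbiome, a fixed effect for taxa needs a response that takes a value for each taxon. A Bray–Curtis distance does not, so the model cannot be fitted to the response that the statistical section names.

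**Working it through.** **1. The primary was planned as continuous.** Inputs from Statistical methods and power calculation: d = 0.4, two-sided alpha 0.05, power 80%, 100 per group.

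n per group = 2(z₀.₉₇₅ + z₀.₈₀)² / d² = 2(1.960 + 0.842)² / 0.16 = 2 × 7.85 / 0.16 = 98.1, so 99.

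The noncentral-t calculation gives 100 per group, with power 0.804. A one-sided test would need 78 and does not match. The stated size is therefore reproduced as a two-sided comparison of two continuous means. Nothing in the article turns area change into a binary outcome.

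**2. Models set side by side.**
- Change in wound area: continuous in its definition and in the power calculation; continuous variables are given t-tests or Wilcoxon tests; interactions are given logistic regression. The last does not fit.
- MALE/MACE: time-to-event in the Abstract and after Figure 1, with Cox named; interactions are given logistic regression. The last departs from Cox and drops time and censoring.
- Major amputation rate and need for new revascularisation: can be handled as binary, so logistic regression can serve.

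**3. What a fitting interaction model could detect.** This is an illustration; the share f of drug users is assumed, equal in both arms, because the article gives none. For a linear model in SD units with 100 per arm:

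SE of the interaction = √[2/(100f) + 2/(100(1 − f))]; power ≈ 1 − Φ(1.96 − D/SE).

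- f = 0.5: SE = √(0.04 + 0.04) = 0.283; power is 0.29 for D = 0.4 and 0.81 for D = 0.8.
- f = 0.3: SE = √(0.0667 + 0.0286) = 0.309; power is 0.25 and 0.74.
- f = 0.2: SE = √(0.10 + 0.025) = 0.354; power is 0.20 and 0.62.

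Even with the right model, an interaction as large as the planned main effect (0.4 SD) would usually be missed. This supports an exploratory label.

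**4. If use after randomisation is meant.** In a simulation with no effect of arm on outcome, drug use was made to depend on arm and on latent severity (users: 50% in one arm, 33% in the other). Arm differences within strata were −0.07 SD in non-users and −0.09 SD in users, where the truth is 0. The apparent interaction was small, −0.088 − (−0.070) = −0.018 SD; the distortion lies mainly in the subgroup contrasts. These sizes depend wholly on the assumed parameters.

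**5. Bray–Curtis has no taxon index.** For samples a and b with abundances over taxa k:

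BC(a, b) = Σₖ|aₖ − bₖ| / Σₖ(aₖ + bₖ).

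Both sums run over k, so the result belongs to a pair of samples. A simulated pair with 50 taxa gives one number, 0.49. There is no per-taxon value for a taxa effect to explain. If the response is the abundance of each taxon, as after Figure 1, there is one value per sample and taxon, and the term fits.

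**The case against.** The strongest reply is that these are supportive analyses. Medication interactions appear among additional outcomes, the microbiome is explanatory, and the article promises to identify exploratory outcomes as such. That stands, and it limits the weight of the point.

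Second, the secondary endpoint is also worded as an incidence, and two further secondary outcomes can be binary. That stands for those outcomes. It does not help the continuous primary, nor MALE/MACE where Cox is named.

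Third, the likeliest fault in the microbiome text is a mislabelled response, since the text after Figure 1 has the model right. That also stands: reconciling the two places is enough, and the microbiome objective as a whole is not beyond estimation.

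Three stronger readings are tempting, and the documents do not support them:
- A reader might infer that the primary comparison loses power through dichotomisation. Logistic regression is named for the interactions, which were never powered; the arm comparison of area change is planned as continuous.
- A reader might infer that drug use is certainly measured on treatment. The word concomitant and the follow-up records point that way, but medication is also recorded at V0 and the article does not say which time point counts.
- A reader might infer that all pairwise distances between samples would be treated as independent. The article never makes them the response; it speaks of changes, with patient random effects, which is compatible with distances from a patient's own baseline.

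**Conclusion.** The point holds as a mismatch between named models and outcomes in two supportive analyses. Logistic regression cannot take the continuous primary without a cut-point that is not stated, and for MALE/MACE it conflicts with the Cox model. A taxa fixed effect cannot enter a model whose response is a Bray–Curtis distance.

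The main arm comparison and the stated sample size, which reproduces, are untouched. No loss of power for the trial can be attached to this point. The consequence is that the interaction analysis leaves an open analyst choice and the beta-diversity model cannot be run as worded. The remark on post-randomisation drug use is conditional on what the sponsor means by antibiotic and concomitant antithrombotic use. The change is worth making before analysis because it is cheap.

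**What to change.** **Interactions.** Replace logistic regression by a linear model for wound area at the last visit, adjusted for baseline area, and a Cox model for MALE/MACE, each with arm-by-medication terms. Keep logistic regression only for outcomes explicitly handled as binary. Label all of these analyses exploratory. Define medication by use recorded at V0. If use after randomisation is intended, say so and report those subgroups as non-randomised and descriptive.

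**Caveat on antibiotics.** State whether the antibiotic exclusion applies to the whole trial or only to the microbiome measures. If it applies to the whole trial, V0 antibiotic use may vary little and that interaction may be barely estimable; the plan should then say what will be reported instead.

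**Microbiome.** Reconcile the statistical section with the text after Figure 1. Keep the taxa-level mixed model for abundance shifts. For beta-diversity, take each patient's Bray–Curtis distance from their own V0 sample as the response, in a mixed model with arm, time, arm × time and a patient random effect, without taxa. PERMANOVA with permutations that respect patient is an optional addition. Since visits are timed from PTA, state whether time in this model runs from V0 or from PTA.

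**Cost.** Changes of wording only. Wound area, medication and wound samples are already scheduled at V0 and at follow-up; no new data or patients are needed.

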## Methods/design

### Study design and randomisation protocol

The PTA-DFS Study is a prospective, monocentric, RCT including participants with T2D and ischemic DFU. Ethics approval was obtained from the local ethics committee (Heinrich Heine University, Düsseldorf, Germany) in accordance with the Declaration of Helsinki (#2022–2291). The PTA-DFS study is registered at www.clinicaltrials.gov (NCT06124586; Registration Date: 2023–08-2).

Participants will be randomly assigned in a 1:1 ratio to either the early PTA group (‘immediate PTA‘ within 48 h after leg artery stenosis (LAS) diagnosis or the elective PTA group (standard of care with PTA within 6 weeks) at the academic hospital of the Heinrich Heine University Düsseldorf, Germany, with inclusion of 200 participants within 5 years. All study participants included in the study will provide informed consent. Although the study is unblinded for both participants and physicians due to practical feasibility, blinding will be applied during the data analysis phase, with separate analysis of primary and secondary endpoints by interventionists (physicians or clinicians) and data analysts to minimise bias. After the data is unblinded, all results will be reviewed collectively. This approach aims to ensure more accurate and unbiased analysis of the primary and secondary endpoints.

Randomisation is performed using a computer-generated sequence with block randomisation to ensure unbiased allocation. The block size will be specified in advance, using blocks of 4 or 6, to maintain balance across groups throughout the study. Both groups receive standard care, with the only difference being the timing of the PTA procedure. The study is structured to ensure that, apart from the timing of PTA, all other aspects of care are consistent across both groups. All subsequent laboratory analyses will be performed in a blinded manner, without knowledge of randomisation. Aside from the timing of PTA, baseline and follow-up examinations will be conducted uniformly across both groups. To optimise recruitment efficiency, training sessions will be held with the interventional angiology staff and the diabetic foot care team, ensuring participants and staff are fully informed about study-related procedures and analyses during their state-of-the-art clinical care.

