### Outcome monitoring

Over the 12-month follow-up period, MALE and MACE are monitored through patient interviews, focusing on vascular events (cardiac, cerebral, peripheral), amputations, infections, sepsis, hospitalisations, and all-cause mortality. For participants unable to attend on-site visits, telephone interviews are conducted to assess complications, including cardiovascular or all-cause mortality.

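### With death and limb loss censored, 1 minus Kaplan–Meier will overstate the 12-month incidence of MALE alone, and of new revascularisation if that is analysed as time-to-event

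*Protocol article*

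**What the plan says.** In the protocol article, the endpoint paragraph of the section Study design and randomisation protocol (after Fig. 1) lists, beside combined MALE and MACE, "time to complete wound healing, major amputation rate and the need for new revascularization". Of these three, only wound healing is worded as a time to an event.

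The section Statistical methods and power calculation adds a separate set of endpoints: "Risk endpoints include the incidence of MALE", together with progression of diabetic complications and length of stay. It assigns this set to survival methods and logistic regression. For time-to-event endpoints in general it states: "Time-to-event clinical endpoints will be analysed with Kaplan–Meier survival curves, while covariate adjustments will be incorporated using Cox proportional hazards models". For categorical variables it offers chi-square or Fisher's exact tests. It names no cumulative-incidence or other competing-risk method.

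The Background describes MALE as limb-specific and MACE as safety-related. The section Outcome monitoring says: "Over the 12-month follow-up period, MALE and MACE are monitored through patient interviews". Those interviews also cover amputations and all-cause mortality, so the competing events are recorded.

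**The concern.** Kaplan–Meier treats a censored participant as someone who could still have the event later. A participant who has died cannot have a later limb event or a new revascularisation. A participant who has lost the limb cannot have that limb treated again. If these participants are censored, 1 minus Kaplan–Meier estimates incidence in a setting where nobody dies or loses a limb, and that exceeds the incidence in the patients actually treated.

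Two things are at stake. One is the reported 12-month incidence of MALE, and possibly of new revascularisation, in a population where deaths and amputations are expected. The other is interpretation: an arm with more deaths or limb losses has fewer limbs left to treat again, so its re-intervention figure needs the competing events beside it.

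**Working it through.** **Inputs from the article.** Allocation: "Participants will be randomly assigned in a 1:1 ratio". Size: "a sample size of n = 100 per group (total n = 200) is required to achieve 80% power at alpha = 0.05". Effect: "Assuming a medium effect size (Cohen's d = 0.4" standard deviations). Follow-up is 12 months. The Background cites limb preservation as high as 94%, that is, about 6% limb loss at best. This is a background figure, not a planning rate.

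**The plan's own figure.** For d = 0.4, two-sided alpha 0.05 and 80% power, n = 2 × (1.960 + 0.842)² / 0.4² = 98.1, so 99 per group. The t-test version gives 99.08, so 100. The stated 100 per group reproduces and is used below for the standard error (SE). The point does not change it.

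**Assumptions.** The article gives no 12-month rate for death, MALE or new revascularisation. I take the true 12-month incidence of the event, c1, as 20–30%, and that of competing events, c2, as 6% (limb loss alone), 16% (with 10% deaths) and 26% (with 20% deaths). Hazards are constant.

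**Formulas.** Total hazard h = −ln(1 − c1 − c2). Event hazard l1 = h × c1/(c1 + c2). With competing events censored, 1 − KM = 1 − exp(−l1). The overstatement is (1 − KM) − c1. The SE of one arm's incidence is √[c1(1 − c1)/100].

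**Worked case, c1 = 25%, c2 = 16%.** h = −ln(0.59) = 0.5276; l1 = 0.5276 × 0.25/0.41 = 0.3217; 1 − KM = 27.5%. The overstatement is 2.5 points. SE = 4.33 points, so the ratio is 0.58.

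| Competing events | Overstatement in points at c1 = 20 / 25 / 30% | In SEs of one arm |
|---|---|---|
| 6% | 0.7 / 0.9 / 1.1 | 0.17 / 0.20 / 0.23 |
| 16% | 2.0 / 2.5 / 3.1 | 0.49 / 0.58 / 0.67 |
| 26% | 3.5 / 4.5 / 5.6 | 0.88 / 1.04 / 1.22 |

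For MALE, major amputation may itself be a component. The competing column should then be read as deaths only.

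**Between arms.** Give both arms the same revascularisation hazard (l1 = −ln 0.70 = 0.357). Let the competing hazard correspond to a 10% risk in one arm and 25% in the other, each taken on its own (l2 = 0.105 and 0.288). Cumulative incidence is l1/(l1 + l2) × [1 − exp(−(l1 + l2))], which gives 28.6% and 26.3%. The arm with more deaths or limb loss shows 2.3 points fewer re-interventions with no effect on re-intervention itself. The SE of the difference is √(0.286 × 0.714/100 + 0.263 × 0.737/100) = 6.3 points, so the shift is 0.36 SE. 1 − KM would be 30% in both arms, and the cause-specific hazard ratio would be 1.

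**The case against.** The strongest case against has five parts.

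- **New revascularisation is not called time-to-event.** A reader might infer that it is certain to be analysed by Kaplan–Meier and Cox. The article does not say so, and a chi-square or Fisher comparison is equally open. This stands, so the point is conditional for that outcome. It is firmer for MALE alone, which the article sends to survival methods, although it does not itemise MALE's components and the absence of death from MALE rests on its description as limb-specific.
- **Limb loss read as freedom from re-intervention.** A reader might infer that Kaplan–Meier both overstates incidence and counts amputees as successes. These come from different handling: overstatement from censoring, the second from keeping those participants event-free in a denominator. Nor does it follow that deaths and amputees must never count as non-events. With complete follow-up, the Aalen–Johansen estimate equals the proportion that does exactly that.
- **Cox is not invalid.** With competing events censored it estimates a legitimate cause-specific hazard ratio. This stands. The ratio only cannot be read as an effect on incidence.
- **Amputation does not make revascularisation impossible.** The article does not limit the outcome to one limb, so treatment of the other leg remains possible. This stands.
- **Size and place.** All rates are assumed. The bias runs the same way in both arms and largely cancels when competing rates are similar. Major amputation and mortality are captured separately. The analysis plan, not shown, may settle the matter. This limits the weight of the point. It does not remove it, because the article itself names the estimator.

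**Conclusion.** The point holds in a limited form. For MALE alone, and for new revascularisation if it is analysed as time-to-event, the named curve estimator overstates 12-month incidence once deaths, and same-limb amputations for re-intervention, are censored. The direction is certain. The size depends on constant hazards and assumed rates: below a quarter of one arm's SE at 6% competing events, and about one SE at 26%. The effect on the comparison between arms is smaller, about a third of an SE in the deliberately unequal example. This affects reported incidence and its interpretation. It is not a flaw in the primary analysis, the sample size or the Cox model.

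**What to change.** 1. State whether new revascularisation is a time-to-event outcome or a proportion, and whether it refers to the same limb.
2. For MALE alone, and for new revascularisation if time-to-event, replace 1 minus Kaplan–Meier with the Aalen–Johansen cumulative incidence. Death is the competing event for both; for same-limb revascularisation, add major amputation of that limb.
3. Keep the planned Cox model and label its result a cause-specific hazard ratio.
4. Report the cumulative incidences and cause-specific hazard ratios of the competing events beside it, so that a lower re-intervention incidence is not read as benefit when it reflects more deaths or limb loss.

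Cost: a few sentences in the analysis plan and a few lines of R, which the trial already uses; no new data and no change in sample size. The downside is one extra table and a slightly lower reported incidence.
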